## Abstract

**Simple Summary:**

A large number of patients with head and neck squamous cell carcinoma (HNSCC) have an advanced-stage disease (stages III to IVB) that do not respond to therapy despite aggressive, site-specific multimodality therapy and most of them will develop disease recurrence. This is the description of a phase IIb randomized multicenter trial that involves the enrolment of 96 patients. The aim of the study is to verify whether electrochemotherapy performed with bleomycin of head and neck squamous cell carcinoma (HNSCC) relapses of the oral cavity and oropharynx is able to lead to an increase in the objective response rate in comparison with the systemic treatment with cetuximab + platinum-based therapy + 5-fluorouracil. The primary objective is to verify the objective response rate of patients in the control arm compared to the treatment arm.

**Abstract:**

Background: A significant proportion of patients with head and neck squamous cell carcinoma (HNSCC) have advanced-stage disease (stages III to IVB) that do not respond to therapy despite aggressive, site-specific multimodality therapy. A great number of them will develop disease recurrence, with up to 60% risk of local failure and up to 30% risk of distant failure. Therapy can be very demanding for the patient especially when important anatomical structures are involved. For these reasons, therapies that preserve organ functionality in combination with effective local tumor control, like electrochemotherapy (ECT), are of great interest. Until few months ago, systemic cetuximab + platinum-based therapy + 5-fluorouracil represented the standard treatment for HNSCC relapses with a median overall survival of 10.1 months and an objective response rate of 36%. Recently the results of KEYNOTE-048 study were published and a new combination of monoclonal antibody named pembrolizumab and chemotherapy emerged as standard first line therapy of recurrent or metastatic tumor that overexpress tissue PDL-1 (Programmed Death 1 ligand). Nevertheless, a variable percentage from 10 to 15% of patients with recurrent/metastatic disease have a tumor that does not overexpress tissue PDL-1, and therefore, according to the results of the KEYNOTE-048 study, does not benefit from replacement of cetuximab with pembrolizumab. These patients will be treated with the “gold standard”: cetuximab, cisplatin/carboplatin and 5-fluorouracil. Aim: To verify whether electrochemotherapy performed with bleomycin of HNSCC relapses of the oral cavity and oropharynx (single relapse on T) is able to lead to an increase in the objective response rate in comparison with the systemic treatment with cetuximab + platinum-based therapy + 5-fluorouracil in patients with PDL-1 negative tumors. Methods: The phase IIb study involves the enrolment of 96 patients who meet the inclusion criteria (48 in the control arm and 48 in the treatment arm). The control arm involves the treatment of HNSCC with systemic treatment (cetuximab + platinum-based therapy + 5-fluorouracil). The treatment arm involves the ECT with bleomycin. The primary objective is to verify the objective response rate of patients in the control arm compared to the treatment arm.

## 1. Introduction

Electroporation (EP) is a technique in which a short and intense electrical field is applied to cells in order to increase the permeability of the cell membrane. As a consequence of the electroporation, molecules that usually cannot enter the cell membrane can reach the cytoplasm through either diffusion or active transport. The combination of cytotoxic drug and EP is called electrochemotherapy (ECT). This study will use the CLINIPORATOR™ (IGEA S.p.A., Carpi, Italy) which induces electroporation by applying electric pulses, thus allowing the transmembrane and intracellular transfer of molecules or compounds for which cell membranes are normally resistant or minimally permeable.

The first electrochemotherapy clinical trials took place at the Institute Gustave Roussy (Villejuif, France) [1,2,3,4]. The Standard Operating Procedures for electrochemotherapy with the Cliniporator™ were established as a result of a European Commission funded project within the 5th framework program [4,5,6,7,8,9]. Subsequent studies have confirmed clinical effectiveness with an acceptable safety profile. Mali et al. included 44 studies and 1894 tumor nodules in their review and meta-analysis and reported that electrochemotherapy had significantly higher effectiveness than bleomycin or cisplatin alone [10]. In their study of electrochemotherapy (bleomycin followed by electroporation) in 85 patients, no serious electrochemotherapy-related adverse events were reported by Campana et al. [8]. Most common adverse events were postoperative pain (92%) and skin reactions (18%) that decreased over time [8].

A significant proportion of patients with head and neck squamous cell carcinoma (HNSCC) have an advanced-stage disease (stages III to IVB) [11] that do not respond to therapy despite aggressive, site-specific multimodality therapy. A great number of them will develop disease recurrence, with up to 60% risk of local failure and up to 30% risk of distant failure [12,13].

Since many patients with relapsed or metastatic disease are unresponsive to therapy, morbidity is high with reduced survival. Palliative systemic therapy with doublet, platinum-based therapy, more effective compared with single agents determine an improvement of response rate but not of survival. A combination of monoclonal antibody (cetuximab or pembrolizumab) and chemotherapy emerged as standard first line therapy of recurrent or metastatic tumors [14]. More in particular, according to the results of the Keynote 048 trial, when pembrolizumab was used alone versus the standard cisplatin-5fluorouracil-cetuximab scheme, patients whose tumor did express high level of tissue PDL-1, experienced a significantly higher OS if compared with standard chemotherapy (14.9 vs. 10.7 months, *p* < 0.0086). On the other hand, patients whose tumor does not express tissue PDL-1, should be yet treated with the combination of cetuximab-platinum and 5-fluorouracil [14], as well as patients with evident contraindications to the use of pembrolizumab.

## 2. Trial Rational

Recurrent extended neoplasms of the head and neck especially if they involve important anatomical structures can be challenging for the surgeon and very demanding for the patient. Surgical treatment of these lesions could be disfiguring and followed by functional impairment. Moreover, chemo-radiotherapy can be associated with anatomical and functional complications, and importantly, radiotherapy has often already been performed up-front, thus limiting the possibility of re-doing it.

For these reasons, therapies like ECT, that preserve organ functionality in combination with effective local tumor control, are of great interest [6,7,8,15,16,17,18,19,20].

ECT has proven to be effective in the treatment of tumors of the skin, subcutaneous and mucosal tissue with several advantages including high success rate in local tumor control (74% complete regression, 11% partial response after one treatment) with limited damage to healthy tissue with good cosmetic and functional results. In fact, surgery and radiotherapy could be associated with not only a scar, but also volume loss, retraction and other deformities, even for small tumors. ECT, by leaving the treated tissue in site for resorption by the body, without stroma and vascular destruction, allows progressive healing with limited compromise of aesthetics or loss of function, with limited side effects and advantageous cost/benefit ratio. In fact, the technology involved and the drug used are not too expansive and the treatment may not require hospitalization since it can be performed under local or general anesthesia. Usually only one session of treatment is required.

The aim of the study is to evaluate efficacy of bleomycin electrotherapy in treatment of recurrent tumors located in the oral cavity and oropharynx in a two arms prospective, randomized, controlled, phase IIb clinical trial.

In this study 96 patients will be enrolled, 48 each arm, which meet the inclusion criteria (patients that need palliative chemotherapy for recurrent HNSCC in the absence of lymph node and systemic metastasis). All patients have primary tumors of the oral cavity, rhino or oropharynx with histological confirmation of local recurrence, with no indication for surgery or irradiation. The patients must have a PDL-1 negative HSNCC or evident contraindications to the use of pembrolizumab.

## 3. Trial Design

Multicenter, two arms, prospective, randomized, controlled, phase IIb clinical trial of intravenous administration of bleomycin combined with electroporation in patients with recurrent squamous cell carcinoma of oral cavity and oropharynx PDL-1 negative or with evident contraindications to the use of pembrolizumab. Patients randomized to the treatment arm that either have their disease progress, locally or systemically, at any point during follow-up will be crossed over to the control arm.

A total of 96 patients (48 patients each arm) will be enrolled.

### 3.1. Objectives

#### 3.1.1. Primary Objective

To verify if the treatment with ECT and bleomycin is superior in terms of objective response to treatment with cetuximab + therapy based on platinum + 5-fluorouracil. The clinical response will be evaluated by RECIST 1.1 criteria on CT and/or MR images at 2 months from baseline.

#### 3.1.2. Secondary Objective

Overall survival;

Evaluation of progression free survival time;

Evaluation of the duration of the response (defined by the interval from the first documentation of a complete or partial response and the onset of disease progression or death);

Evaluation of disease control, defined as complete response, partial response and stable disease between the two groups;

The quantification of the impact of treatment on the patient quality of life, in terms of pain reduction and bleeding.

### 3.2. Inclusion and Exclusion Criteria

Before enrolment investigators will assess the eligibility of the patients. When a patient is eligible for participation, detailed study information will be provided. The patients who decide to participate in the study will sign informed consent witnessed by a member of the research group. Inclusion and exclusion criteria are summarized in Table 1.

### 3.3. Control Group Treatment

In the control group, patients whose tumor does not express tissue PDL-1 will be treated with the combination of cetuximab, cisplatin/carboplatin and 5-fluorouracil. In addition, patients with evident contraindications to the use of pembrolizumab, in the opinion of the investigator, can be enrolled in this Protocol.

Carboplatin (AUC 5 IV day 1) or cisplatin (at a dose of 100 mg/m^2^) and cetuximab (at a dose of 400 mg/m^2^), as a 2 h intravenous infusion (loading dose), then 250 mg/m^2^, as an infusion intravenously 1 h per week per day 1 and 5-FU (at a dose of 1000 mg/m^2^ per day for 4 days) every 3 weeks followed by maintenance of cetuximab with 250 mg/m^2^ every week or 500 mg/m^2^ every 2 weeks.

### 3.4. Experimental Group Treatment

Each patient will be subjected to electrochemotherapy with bleomycin. ECT is a combination treatment including the injection of an anticancer drug (bleomycin) followed by the delivery of electric pulses using appropriate electrodes and electric pulses. Bleomycin will be injected intravenously to ensure that the whole tumor field will be infiltrated by the drug and that the concentration of bleomycin in the interstitial tissue will be sufficient to kill all the dividing tumor cells while completely sparing the normal non-dividing cells.

Bleomycin is active on any type of tumor because electroporation affects all the cell types and, once cells are electro-permeabilized, it can enter all the cells and interact with the cell DNA in the same way whatever the cell type and whatever the genetic expression of the cell.

Bleomycin will be prepared in the pharmacy of each Institution using the standard procedures for this drug. It will be injected in an intravenous bolus over a short time, up to 5 min at a dose of 15,000 IU/m^2^.

Appropriate electrodes will be inserted in and around the lesions 8 min after the end of the bolus injection of bleomycin. The electric pulses are generated by a Cliniporator™ (IGEA SpA, Carpi, Italy) and will be delivered by means of appropriate electrodes. Both the electrodes and pulse generator have CE certification. ECT treatment will be performed according to ESOPE protocol [5,6].

#### ECT Procedure

Cliniporator™ (IGEA S.p.A., Italy) will be used to deliver electric voltage with the following parameters: 8–96 pulses of 140–1000 V, of 100 μs duration, at 5000 Hz repetition frequency. The electrodes will be chosen between linear, hexagonal, finger and expandable deployable endoscopic ones depending on the size and tumor localization. Generally, linear needle electrodes will be used to treat cutaneous, lymph node and subcutaneous lesions smaller than 3 cm while use of the hexagonal will be limited in wider tumors. Finger and expandable deployable endoscopic electrodes will be used to reach less accessible lesions, such as those localized in the oro-pharynx (tonsil and base of tongue). The surgeon will perform multiple procedures of the electrode in the tumor tissue covering the complete area of the lesion to be treated and possibly a margin area of free tissue growths of 3–5mm (overtreatment) around the lesion itself. The procedure can require one or more electrode insertion and pulse applications and must be completed within 40 min from the end of bleomycin injection.

If the procedure will be performed under local anesthesia, the last will be induced between bleomycin injection and the beginning of the electrode’s insertion; while if the procedure will be performed under general anesthesia, bleomycin injection will follow the induction of anesthesia itself.

The patients will be randomized 1:1 to ECT or standard treatment.

In Figure 1 the treatment in the two arms of treatment is schematically represented.

### 3.5. Endpoints Evaluation Criteria

#### 3.5.1. Primary Outcome Measures

To verify if the treatment with ECT and bleomycin is superior in terms of objective response to treatment with cetuximab + therapy based on platinum + 5-fluorouracil. Tumor response will be evaluated by means of clinical and radiological examination. Biopsy with histological examination is performed on indication [21].

In case of progression disease (local or systemic): revaluation of the lesion stage will be done and crossover to control arm would be considered. The appearance of one or more new lesions is also considered progression.

In case of stable disease or partial response: revaluation of the lesion stage and the possibility of a second treatment with ECT will be considered.

Objective evaluation of tumor response will be performed in accordance with RECIST criteria (version 1.1) [22].

The events that eventually occur in the course of the treatment period and/or the follow up, attributable or not to the research, will be considered an adverse event (AE) and will be registered on the applicable case report form. Intercurrent events are any clinical or biological abnormalities not present at the start of the trial. The events will be identified either through patients’ spontaneous statements or following questioning by the researcher and during the examinations.

The National Cancer Institute’s Common Toxicity Criteria for Adverse Events, version 4.0 (CTCAEv4) will be used to estimate the toxicity [26].

### 3.6. Duration of the Study and Follow Up

The study will last 48 months and the patients will be followed up for a minimum of 12 months.

The patients will be visited 1, 2, 4, 6, 8, 10, and 12 months after the treatment. CT/MRI or PET-CT will be performed at 2, 6 and 12 months from treatment. The cut-off point for tumor response evaluation has been fixed at 2 months. The visits scheme is showed in Table 2.

### 3.7. Description of Study Procedures

#### 3.7.1. Visit 1

Patients must sign individual informed consent form before they undergo any study procedures. Patients who fulfil all inclusion criteria and do not meet any exclusion criteria will be enrolled.

At Visit 1, patients will be interviewed and their study eligibility determined according to the inclusion and exclusion criteria and then will be randomized 1:1 to ECT or standard treatment. The investigator will collect and document the patient’s medical history with special emphasis on oncology history, previous chemotherapy, and response to prior therapy. Patients will be asked about concomitant treatments, medications, and events at each patient contact and each visit. Treatment information will include nature of treatment, start date, end date, and reason for treatment. Drug information gathered and documented will include dose, route of administration, frequency, start date, end date, and indication, as applicable. Continuation and discontinuation of treatments and drugs will be verified with the patient at each visit.

The patient will undergo a comprehensive physical examination that includes weight, height, and vital signs. Patients observed with an active infection of any kind will be excluded from study participation.

The ECOG (Eastern Cooperative Oncology Group) Performance Status [27] will be evaluated as inclusion criteria: patients who are grades 0, 1 or 2 are eligible for study participation.

CBC and coagulation profiles will be measured at the enrolment visit (Visit 1). Patients with an absolute neutrophil count below 1000/mL, platelet count below 70,000/mL, and/or INR above 1.5 will be excluded from study participation.

Pain will be assessed at all visits using a 100 mm anchored visual analogy scale with 0 being “No Pain” and 100 mm being “Pain as bad as it could possibly be.”

EORTC QLQ-C30, EORTC QLQ-H&N35, EQ5d questionnaires, will be completed at each follow up visit to measure the patient’s quality of life.

All patients will undergo pre-anesthesia assessment in accordance with the usual and customary anesthesia assessment procedures at the clinical site. Patients found not to be acceptable for either general anesthesia or monitored anesthesia care (conscious sedation) will be excluded from study participation.

#### 3.7.2. Visit 2

After confirmation of continued study eligibility, the day of the treatment the patients will be undergo ECT treatment (treatment group) or directly to cetuximab + platinum + 5-fluorouracil therapy (control group).

Patients randomized to treatment group will undergo ECT treatment in accordance with established clinical and institutional practices.

Pain will be assessed immediately before discharge from the treatment facility. Patients will be encouraged to report symptoms to investigators at any time but will be specifically queried and evaluated for toxicity and adverse events at each visit.

The use of general anesthesia or monitored anesthesia care (conscious sedation with local anesthesia) will be determined by the anesthesiologist based on usual and customary practices for invasive procedures at the respective clinical site.

In the treatment arm, after induction of anesthesia or sedation, the patient will be prepared and draped for the electroporation procedure according to usual and customary procedures for invasive surgical procedures.

Once the lesion has been treated, the usual and customary wound dressing will be applied and the patient will be transferred to post-anesthesia care for further monitoring and pain management. Toxicity and adverse events due to bleomycin will be evaluated after recovery from anesthesia/conscious sedation.

Post-procedure analgesia is prescribed by the investigator in accordance with usual and customary practices at the respective clinical site. Recording of the drugs used for pain control will be done.

The investigator will establish the need for post-procedure hospitalization on the base of the patient’s response to the electrochemotherapy and anesthesia/monitored anesthesia (conscious sedation) care, as well as usual and customary clinical practice at the study site. Routine post procedure hospitalization, therefore, is not considered an adverse event.

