## Figures and Tables

**Figure 1 cancers-13-02210-f001:**
[figure not shown]
Trial design flowchart.

**Table 1 cancers-13-02210-t001:** Inclusion and exclusion criteria.

Inclusion Criteria	Exclusion Criteria
Age ≥ 18 years	Age < 18 years
Progressive disease (single recurrence on T and N0) of oral cavity or oropharynx. Absence of other systemic metastases in any site outside the locoregional recurrence	Other symptomatic lesions not under control
Histological diagnosis of squamous cell carcinoma	Lesions not suitable for ECT (bone invasion, large vessels infiltration, etc.)
Measurable lesions suitable for application of electric pulses	Lesions not eligible for systemic treatment with cetuximab + platinum + 5-fluorouracil therapy
Performance status (Karnofsky ≥ 70; WHO ≤ 2)	Acute lung infection
Life expectancy> 3 months	Symptoms of poor lung function
Ability to understand the information given and sign informed consent	Non-correctable severe coagulation disorders
Patients must have offered standard treatments	Previous allergic reactions to bleomycin
	Previous cumulative dose of 250 mg/m^2^ of bleomycin exceeded
	Chronic renal dysfunction (creatinine> 150 µmol/L must be considered a lower administered dose of bleomycin)

**Table 2 cancers-13-02210-t002:** Visits scheme.

Visit		1	2		3	4	5	6	7	8	9
Time		Month -1 (up to 1 month prior the treatment)	Month 0		Month 1 ± 1 week	Month 2 ± 1 week	Month 4 ± 1 week	Month 6 ± 1 week	Month 8 ± 1 week	Month 10 ± 1 week	Month 12 ± 1 week
	Visit Description	Restaging, enrolment, randomization	Day of treatment Control group: cetuximab + platinum + 5- fluorouracil Treatment group: electrochemotherapy	Post treatment evaluation (discharge day ± 1 week)	Follow up visit	Follow up visit Cut off time to evaluate treatment response	Follow up visit	Follow up visit	Follow up visit	Follow up visit	Follow up visit
Type of assessment											
Clinical evaluation			X	X	X	X	X	X	X	X	X
Duration of hospitalization				X							
CT, MRI or PET-CT		X	Estimation of Lesion size and assignment of T stage			X		X			X
Identification of the target lesion		X	X	X							
Photographic documentation		X	X		X	X	X	X	X	X	X
EORTC QLQ-C30, EORTC QLQ-H&N35, EQ-5D-5L questionnaires		X		X	X	X	X	X	X	X	X
Pain evaluation with VAS score		X		X	X	X	X	X	X	X	X
Blood samples as per normal clinical practice		X	X		X	X	X	X	X	X	X
CD8 and CD16 dosage			X		X	X	X	X			
Recording of the drugs for pain control				X		X	X	X	X	X	X
Recording of concomitant treatment					X	X	X	X	X	X	X

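### The neutrophil and platelet exclusion limits in Section 3.7.1 are printed per mL, a factor of 1000 from a per-µL reading, so as written they would exclude essentially no one

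*Protocol article*

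**What the plan says.** Section 3.7.1 (Visit 1) of the protocol article sets the laboratory exclusions at enrolment: "Patients with an absolute neutrophil count below 1000/mL, platelet count below 70,000/mL, and/or INR above 1.5 will be excluded from study participation". The same section adds a general infection rule: "Patients observed with an active infection of any kind will be excluded from study participation". It enrols only patients who meet every inclusion criterion and no exclusion criterion.

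Section 3.2 says that Table 1 summarises the criteria. Table 1 has no row for neutrophils, platelets or INR. Its coagulation exclusion reads "Non-correctable severe coagulation disorders", and its infection exclusion is confined to acute infection of the lung.

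On primary site, Section 2 states: "All patients have primary tumors of the oral cavity, rhino or oropharynx with histological confirmation of local recurrence". The corresponding row of Table 1 reads "Progressive disease (single recurrence on T and N0) of oral cavity or oropharynx".

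On PD-L1, Section 2 states: "The patients must have a PDL-1 negative HSNCC or evident contraindications to the use of pembrolizumab". Section 3 (Trial Design) and Section 3.3 (Control Group Treatment) give the same condition. Table 1 has no row for it.

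**The concern.** An exclusion limit works only if a plausible patient can fall below it. Read literally, the two count limits lie so far below ordinary blood counts that they are inert. They are checked before electrode insertion in one arm and before platinum with 5-fluorouracil in the other, so they are safety-related. An eligibility form or database check that copied the printed numerals and unit would let a patient with a very low count through on these two items without a flag.

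A smaller matter is that the eligibility text and its summary table differ in scope on coagulation and on infection, and that one sentence in Section 2 names a primary site that no other section names. In a multicentre trial, a site that works from the table and a site that works from the visit description could decide differently on the same patient.

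**Working it through.** **Unit conversion**

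Inputs, both from Section 3.7.1: a neutrophil limit of 1000 per mL and a platelet limit of 70,000 per mL. These limits are set, not derived from other figures, so there is no calculation in the plan to reproduce.

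Formula: count per µL = count per mL ÷ 1000, because 1 mL = 1000 µL. Count per litre = count per mL × 1000.

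- Neutrophils: 1000 ÷ 1000 = 1 per µL; 1000 × 1000 = 10⁶ per L = 0.001 × 10⁹/L.
- Platelets: 70,000 ÷ 1000 = 70 per µL; 70,000 × 1000 = 7 × 10⁷ per L = 0.07 × 10⁹/L.

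With the same numerals per µL, the limits would be 1.0 × 10⁹/L and 70 × 10⁹/L, which is 1000 times the printed ones. This shows only the size of the discrepancy and does not propose a threshold.

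**Do the printed limits ever operate?**

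The article gives no reference range, so the counts below are assumed and reach down to very low values.

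| Assumed count | Same count per mL | Below the printed limit? | Below the same numeral per µL? |
|---|---|---|---|
| Neutrophils 10/µL | 10,000 | No (10 times the limit) | Yes |
| Neutrophils 500/µL | 500,000 | No | Yes |
| Neutrophils 2000/µL | 2,000,000 | No | No |
| Platelets 1,000/µL | 1,000,000 | No (about 14 times the limit) | Yes |
| Platelets 50,000/µL | 50,000,000 | No | Yes |
| Platelets 150,000/µL | 150,000,000 | No | No |

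No assumed count is excluded as printed. A neutrophil count of zero would still be caught, which is why the wording here is *essentially no one*. The INR part, "and/or INR above 1.5 will be excluded from study participation", does not depend on the unit and works as printed.

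**Is it a text-reading artefact?**

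This cannot be ruled out entirely but is unlikely. The micro sign survives elsewhere in the same text, in the pulse duration under ECT Procedure and in the creatinine row of Table 1. The unit mL also appears for both counts in the sentence. No other section gives the limits in a different unit.

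**Scope, side by side**

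| Item | Text | Table 1 | Patient treated differently |
|---|---|---|---|
| Coagulation | Any INR above 1.5 (Section 3.7.1) | Only severe disorders that cannot be corrected | A correctable INR above 1.5 |
| Infection | Any active infection (Section 3.7.1) | Only acute infection of the lung | An active infection outside the lung |
| Primary site | Section 2 adds *rhino* | Oral cavity or oropharynx | A rhinopharyngeal primary |

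The Simple Summary, the Abstract, the aim sentence in Section 2 itself, Section 3 and the Conclusions agree with Table 1 on site.

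**The case against.** The strongest reply is that this is an obvious slip in a journal article. The limits are so implausible as printed that a clinician would notice, and the full protocol and the working eligibility form are not shown and may have the unit right. That is fair as to likely harm, and it is not known that any site would apply the literal value. It does not remove the point. The article states the limits wrongly, which is different from leaving a detail out, and its Data Availability statement says that all protocol data are in the manuscript.

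A second reply is that the criteria are cumulative. The INR rule and the coagulation row of Table 1 can both apply, and so can the two infection rules. That stands: they are not logically incompatible. Applied together, the broader rule governs, and the table then describes a narrower exclusion than the one in force. This calls for alignment of wording.

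A third reply is that laboratory limits missing from a table described as a summary are ordinary condensation. That also stands, and the absence of count and INR rows is not held against the plan.

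Two stronger readings are tempting, and the article does not support them:

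- A reader might infer that the enrolment checks as a whole would pass every patient. They would not. The INR, infection and anaesthesia exclusions in Section 3.7.1 still operate, Table 1 excludes cases not eligible for the control regimen, and eligibility is confirmed again on the treatment day (Section 3.7.2).
- A reader might infer from Table 1 that PD-L1 status is not an entry condition. Sections 2, 3 and 3.3 all state it and nothing contradicts it, so the missing row is a minor alignment point.

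**Conclusion.** The point holds for the two count limits. As printed they equal 1 neutrophil and 70 platelets per µL, a factor of 1000 below a per-µL reading of the same numerals. The conversion is exact. The conclusion that they would exclude essentially no one rests on the stated assumption about usual blood counts. Nothing in the article corrects the unit. It looks like a printing slip, but the article alone cannot show which unit or values were intended.

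The differences on coagulation and infection, and the single mention of *rhino*, are smaller mismatches to settle in the same correction. The primary endpoint, significance level, sample size and power are untouched.

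**What to change.** The sponsor confirms the intended unit and values of the neutrophil and platelet limits and corrects Section 3.7.1, together with any eligibility form or edit check built on it.

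The same clarification should:

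- reconcile Section 3.7.1 and Table 1 on coagulation and on infection, so that each has one stated scope;
- reconcile the list of primary sites in Section 2 with the oral cavity and oropharynx population stated elsewhere;
- for consistency, add to Table 1 the PD-L1 or pembrolizumab condition already given in Sections 2, 3 and 3.3.

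The sponsor's clinicians decide the values and the scope; this review proposes none. The cost is a short clarifying amendment and a check of the eligibility form. No statistical recalculation is needed.
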